# INTRODUCTION AND BACKGROUND

# Background and rationale

Recent years have seen a widespread uptake of respiratory (and gastro-intestinal) pathogen molecular diagnostic tests that test for multiple potential pathogens for each sample. Not only does this increase the breadth or organisms tested for, but the increased sensitivity of this testing for DNA or RNA of these organisms has vastly increased the number of positive tests.

This has allowed the availability of surrogate population level data regarding the distribution of many common pathogens across time and place, with most hospitals and community pathogen providers in Victoria utilising these assays. It is now feasible technically to de-identify these data and amalgamate all results to improve our understanding of how these organisms circulate each year.

At the same time, our ability to examine location specific health events from multiple levels of health care provision has improved. These include calls to telephone health advice lines, general practitioner (GP) presentations, ambulance encounters, emergency department presentations and hospital admission data.

This now means we have the opportunity to examine associations between potential pathogens and patterns of health care presentations using geo-temporal statistical methodologies with completely deidentified, non-linked data. This has the advantage of observing all patients’ privacy while still having the potential to upload, aggregate and examine real-time data.

1. STUDY OBJECTIVES AND OUTCOMES

# Objectives

The objectives of this study are:

To examine and describe organism specific epidemiology of respiratory and gastrointestinal positive tests from all participating laboratories.

To describe the association of organisms in time and place with health service utilisation and presentations.

# Primary objective

To describe the retrospective and ongoing prospective geo-temporal organism and age specific epidemiology of de-identified respiratory and gastrointestinal multiplex polymerase chain reaction (PCR) positive results from all participating laboratories across Victoria.

# Secondary objectives

The secondary objectives of this study are:

To use retrospective data, to evaluate the geo-temporal association of organism specific activity with health outcomes and health service utilisation from multiple levels of healthcare, including hospital admission and emergency presentations, ambulance service provision, GP presentations and telephone health advice requests.

To publish the organism specific epidemiology for continuously updated open access, for example on a website accompanied with related health information for community members and primary care practitioners.

# 4. STUDY DESIGN AND METHODOLOGY

# 4.1. Study design schema

This study will be conducted in two phases. First, the retrospective phase will involve collection, synthesis, and analysis of retrospective data to establish appropriate statistical analysis methodologies and potential approach to prospective data. Following establishment of this methodology, the prospective phase will begin, applying the modelling techniques developed in the retrospective phase.

# 4.2. Study Schema

[figure not shown]

# 4.3. Retrospective Study Design

### 4.3.1. Microbiology extraction and de-identification

Retrospective results for multiplex PCR assays and other upper airway specimens (e.g., throat swab culture) will be extracted from each pathology system within each organisation’s firewall, then de-identified, with further potentially identifiable information being aggregated (e.g., birthdates calculated into closest year of age).

### 4.3.2. Microbiology results secure uploading

De-identifiable aggregated fields for each pathology tests will be uploaded into a secure REDCap

database with multi-factor authentication. The uploaded fields will be:

- Age in years (or less than one year of age: <6m, 6m-11m)
- Postcode of residence
- Gender
- Date of test
- All positive results for that test (e.g., RSV and influenza positive)

### 4.3.3. Clinical presentation data extraction and de-identification

The following table delineates the intended datasets for inclusion into the SNOTWATCH project. Refer to Appendix 16.1. for the requested variables for each dataset.

| Victorian Hospital Admission Data | Data will be obtained from the Victorian Admitted Episode Dataset (VAED) regarding acute admissions for conditions potentially related to respiratory infections or gastrointestinal infections, including (but not limited to) pneumonia, exacerbations of chronic obstructive pulmonary disease, asthma, bronchiolitis, gastroenteritis, fever, febrile convulsions, encephalitis, sepsis, invasive Group A streptococcal disease and acute myocardial episodes. As other opportunities arise, arrangements will be made to bring additional data sources into the SNOTWATCH initiative, depending on their relevance to specific conditions e.g., BloodSTAR for intravenous immunoglobulin usage for Kawasaki disease). |
| --- | --- |
| Victorian Emergency Department Presentation Data | Data will be obtained from a variety of emergency department data sources.  Retrospective data will be obtained from the Victorian Emergency Minimum Dataset (VEMD) regarding acute admissions for conditions potentially related to respiratory infections or gastrointestinal infections, including (but not limited to) pneumonia, exacerbations of chronic obstructive pulmonary disease, asthma, bronchiolitis, gastroenteritis, fever, febrile convulsions, encephalitis, sepsis, invasive Group A streptococcal disease and acute myocardial episodes. |
| Site-specific Emergency Department Presentation Data | ED department software will be accessed from Victorian hospitals including (but not limited to) Alfred Health (Cerner), Monash Health (Symphony), the Royal Children’s Hospital (Epic) for presentations potentially related to respiratory infections or gastrointestinal infections, including (but not limited to) pneumonia, exacerbations of chronic obstructive pulmonary disease, asthma, bronchiolitis, gastroenteritis, fever, febrile convulsions, encephalitis, sepsis, invasive Group A streptococcal disease and acute myocardial episodes. |
| Rapid Health Emergency Medicine Monitoring System (RHEMMS) | RHEMMS, currently under development at DHHS Victoria, is a near real-time emergency department system centralising information from many Victorian EDs. Originally developed to detect a further episode of thunderstorm asthma activity increase as soon as possible, limited information regarding all presentations is proposed to be de-identified, encrypted and sent to the RHEMMS server in the secure DHHS Azure cloud. |
| POLAR GP General practice presentation data | Outcome Health’s POLAR GP is a collaboration between Outcome Health and participating Primary Health Networks (PHNs) that provides quality benchmark information to each practice and PHN, as well as relevant business relevant information back to each practice. De-identified data from consented general practices within participating Primary Health Networks is extracted using the “Hummingbird” extraction system from common primary care software (e.g. Best Practice, Medical Director). This data is then stored at a secure, central data warehouse. Data stored in the data warehouse is not re-identifiable outside of the GP practice it originated from, but multiple encounters by the same individual are recorded as being by the same person. Presentation diagnosis data (if entered) is classified into SNOMED categories. |
| Tele-health Data | Telephone health advice data (HealthDirect, Nurse-on-Call) is logged from telephone calls from consumers into a categorical and free text database by trained nurses. |
| Ambulance Victoria data | De-identified data from Ambulance Victoria data will be obtained from calls to ambulance Victoria recorded by telephone triage staff and ambulance attendances recorded by ambulance officers. |
| Victorian Hospital Admission Data | Data will be obtained from the Victorian Admitted Episode Dataset (VAED) regarding acute admissions for conditions potentially related to respiratory infections or gastrointestinal infections, including (but not limited to) pneumonia, exacerbations of chronic obstructive pulmonary disease, asthma, bronchiolitis, gastroenteritis, fever, febrile convulsions, encephalitis, sepsis, invasive Group A streptococcal disease and acute myocardial episodes. As other opportunities arise, arrangements will be made to bring additional data sources into the SNOTWATCH initiative, depending on their relevance to specific conditions e.g., BloodSTAR for intravenous immunoglobulin usage for Kawasaki disease). |
| Victorian Emergency Department Presentation Data | Data will be obtained from a variety of emergency department data sources.  Retrospective data will be obtained from the Victorian Emergency Minimum Dataset (VEMD) regarding acute admissions for conditions potentially related to respiratory infections or gastrointestinal infections, including (but not limited to) pneumonia, exacerbations of chronic obstructive pulmonary disease, asthma, bronchiolitis, gastroenteritis, fever, febrile convulsions, encephalitis, sepsis, invasive Group A streptococcal disease and acute myocardial episodes. |
| Site-specific Emergency Department Presentation Data | ED department software will be accessed from Victorian hospitals including (but not limited to) Alfred Health (Cerner), Monash Health (Symphony), the Royal Children’s Hospital (Epic) for presentations potentially related to respiratory infections or gastrointestinal infections, including (but not limited to) pneumonia, exacerbations of chronic obstructive pulmonary disease, asthma, bronchiolitis, gastroenteritis, fever, febrile convulsions, encephalitis, sepsis, invasive Group A streptococcal disease and acute myocardial episodes. |
| Rapid Health Emergency Medicine Monitoring System (RHEMMS) | RHEMMS, currently under development at DHHS Victoria, is a near real-time emergency department system centralising information from many Victorian EDs. Originally developed to detect a further episode of thunderstorm asthma activity increase as soon as possible, limited information regarding all presentations is proposed to be de-identified, encrypted and sent to the RHEMMS server in the secure DHHS Azure cloud. |
| POLAR GP General practice presentation data | Outcome Health’s POLAR GP is a collaboration between Outcome Health and participating Primary Health Networks (PHNs) that provides quality benchmark information to each practice and PHN, as well as relevant business relevant information back to each practice. De-identified data from consented general practices within participating Primary Health Networks is extracted using the “Hummingbird” extraction system from common primary care software (e.g. Best Practice, Medical Director). This data is then stored at a secure, central data warehouse. Data stored in the data warehouse is not re-identifiable outside of the GP practice it originated from, but multiple encounters by the same individual are recorded as being by the same person. Presentation diagnosis data (if entered) is classified into SNOMED categories. |
| Tele-health Data | Telephone health advice data (HealthDirect, Nurse-on-Call) is logged from telephone calls from consumers into a categorical and free text database by trained nurses. |
| Ambulance Victoria data | De-identified data from Ambulance Victoria data will be obtained from calls to ambulance Victoria recorded by telephone triage staff and ambulance attendances recorded by ambulance officers. |

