| Victorian Hospital Admission Data | Data will be obtained from the Victorian Admitted Episode Dataset (VAED) regarding acute admissions for conditions potentially related to respiratory infections or gastrointestinal infections, including (but not limited to) pneumonia, exacerbations of chronic obstructive pulmonary disease, asthma, bronchiolitis, gastroenteritis, fever, febrile convulsions, encephalitis, sepsis, invasive Group A streptococcal disease and acute myocardial episodes. Other de-identified data fields will also be included as opportunities arise and arrangements will be made to bring additional data sources into the SNOTWATCH initiative, depending on their relevance to specific conditions e.g., BloodSTAR for intravenous immunoglobulin usage for Kawasaki disease). |
| Victorian Emergency Department Presentation Data | Data will be obtained from a variety of emergency department data sources.  Retrospective data will be obtained from the Victorian Emergency Minimum Dataset (VEMD) regarding acute admissions for conditions potentially related to respiratory infections or gastrointestinal infections, including (but not limited to) pneumonia, exacerbations of chronic obstructive pulmonary disease, asthma, bronchiolitis, gastroenteritis, fever, febrile convulsions, encephalitis, sepsis, invasive Group A streptococcal disease and acute myocardial episodes. |
| Site-specific Emergency Department Presentation Data | ED department software will be accessed from Victorian hospitals including (but not limited to) Alfred Health (Cerner), Monash Health (Symphony), the Royal Children’s Hospital (Epic) for presentations potentially related to respiratory infections or gastrointestinal infections, including (but not limited to) pneumonia, exacerbations of chronic obstructive pulmonary disease, asthma, bronchiolitis, gastroenteritis, fever, febrile convulsions, encephalitis, sepsis, invasive Group A streptococcal disease and acute myocardial episodes. |
| Rapid Health Emergency Medicine Monitoring System (RHEMMS) | RHEMMS, currently under development at DHHS Victoria, is a near real-time emergency department system centralising information from many Victorian EDs. Originally developed to detect a further episode of thunderstorm asthma activity increase as soon as possible, limited information regarding all presentations is proposed to be de-identified, encrypted and sent to the RHEMMS server in the secure DHHS Azure cloud. |

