# APPENDIX

## 16.1. Requested variables from each dataset

| **State or Territory Dataset** | |
| --- | --- |
| **Name of state or territory dataset:** | Victorian Emergency Minimum Dataset |
| **Data custodian:** | Department of Health (Victoria) |
| **Data requested for the period** | Ongoing |
| **Requested variables** | |
| ICD10AM Discharge Code/s | Age band according to VAED criteria |
| Patient residence location by statistical area (SA2 or SA3) | Date of presentation |
| Gender |  |

| **State or Territory Dataset** | |
| --- | --- |
| **Name of state or territory dataset:** | Victorian Admitted Episodes Dataset |
| **Data custodian:** | Department of Health (Victoria) |
| **Data requested for the period** | Ongoing |
| **Requested variables** | |
| ICD10AM Discharge Code/s | Age (Years, or if less than one year of age: <6m, 6m-11m) |
| Patient residence location by statistical area (SA2 or SA3) | Date of admission |
| Gender |  |

| **State or Territory Dataset** | |
| --- | --- |
| **Name of state or territory dataset:** | Tele-health Triage Calls |
| **Data custodian:** | Ambulance Victoria |
| **Data requested for the period** | Ongoing |
| **Requested variables** | |
| Age (Years, or if less than one year of age: <6m, 6m-11m) | Primary complaint/reason or call category |
| Caller location by postcode or statistical area 2 or 3 | Date of call |
| Gender of consumer call | Free text from primary complaint notes |
| Presence of specific categorical recorded solicited symptoms (e.g., fever/respiratory distress/ chest pain) | Categorical nature of advice given (home care/GP phone transfer/ advice to see GP/advice to attend ED/Ambulance called) |

| **State or Territory Dataset** | |
| --- | --- |
| **Name of state or territory dataset:** | Ambulance attendances |
| **Data custodian:** | Ambulance Victoria |
| **Data requested for the period** | Ongoing |
| **Requested variables** | |
| Diagnosis code/s or categories | Age (Years, or if less than one year of age: <6m, 6m-11m) |
| Patient residence location by statistical area or postcode | Date of presentation |
| Gender | Free text entry regarding presenting complaint |
| Presentation classification | Treatment given |

| **State or Territory Dataset** | |
| --- | --- |
| **Name of state or territory dataset:** | Tele-health Triage Calls |
| **Data custodian:** | Nurse on Call |
| **Data requested for the period** | Ongoing |
| **Requested variables** | |

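### The protocol gives two incompatible scopes for VEMD, its statewide retrospective ED source: admissions in the extraction rows, all presentations elsewhere

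*Protocol*

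**What the plan says.** The tables in Sections 4.3.3 and 4.4.1.2 list the datasets to be obtained. Each table prints its rows twice, so the VEMD row appears four times, always with the same scope. In Section 4.3.3 it reads "Retrospective data will be obtained from the Victorian Emergency Minimum Dataset (VEMD) regarding acute admissions for conditions potentially related to respiratory infections", and in Section 4.4.1.2 "Retrospective data will be obtained from the Victorian Emergency Minimum Dataset (VEMD) regarding acute admissions". The row is labelled "Victorian Emergency Department Presentation Data".

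The VAED row uses the same phrase and the same condition list: "Data will be obtained from the Victorian Admitted Episode Dataset (VAED) regarding acute admissions for conditions potentially related to respiratory infections". The site-specific ED row keeps the condition list but changes the event: "for presentations potentially related to respiratory infections or gastrointestinal infections". The RHEMMS row is also about presentations: "limited information regarding all presentations is proposed to be de-identified, encrypted and sent to the RHEMMS server".

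The secondary objectives name the levels of care to be studied, "including hospital admission and emergency presentations, ambulance service provision, GP presentations and telephone health advice requests". Section 4.5.7 includes every VAED and VEMD record and every ED encounter in the participating datasets. Section 4.5.8 allows one exclusion only, opting out of POLAR GP. In Appendix 16.1 the date requested for VEMD is "Date of presentation", whereas for VAED it is the admission date.

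**The concern.** An ED presentation and an acute admission are different events. Some patients who present are admitted, and the rest go home. The secondary objective treats the two as separate outcomes, but the VEMD extraction row describes the ED dataset in terms of admissions.

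This matters because of VEMD's place in the study. Section 4.5.6 says that VAED and VEMD together capture more than 95% of episodes of care in Victoria, while full ED data will come from three hospital networks only. RHEMMS is described as still under development. VEMD is thus the statewide ED source for the retrospective phase.

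A custodian or analyst working from the extraction row could deliver or select admitted patients only. The association of organisms with ED presentations would then be estimated statewide on admitted visits and at the three networks on all visits, under one heading. Section 4.1 also says that methods developed retrospectively will be applied prospectively, where VEMD is not used and the remaining ED sources are worded as presentations. The retrospective baseline could then count a different event from the prospective series.

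**Working it through.** No arithmetic applies. The protocol states no figure that depends on the VEMD scope, so the check is a comparison of the places that bear on it.

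**Pointing to admissions only**
- The VEMD row, four times, in Sections 4.3.3 and 4.4.1.2.

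**Pointing to all presentations**
- The label of that same row.
- The secondary objectives, which list admissions and emergency presentations as distinct levels of care.
- Section 4.5.7, which takes all VEMD records.
- Section 4.5.8, which has no exclusion for patients who were not admitted.
- Appendix 16.1, which keys VEMD to the presentation date and VAED to the admission date.

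**Neighbouring sources, for comparison**
- Site-specific ED and RHEMMS are both worded as presentations, so the admission wording affects VEMD alone.

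**Does one statement clearly override the other?** No. Section 4.5.7 is broad, but the extraction rows already narrow it by condition, so it cannot simply be read as cancelling whatever those rows say. Equally, the extraction row cannot be read as a deliberate restriction when its own label and the objective it serves say otherwise.

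**Would the delivered data show which scope was used?** No. The VEMD list in Appendix 16.1 holds ICD-10-AM discharge codes, age band, residence by SA2 or SA3, presentation date and gender. None of these separates admitted from discharged visits. If the custodian filtered on admission before delivery, the extract would look the same in structure.

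**Size under the literal reading.** If a share *p* of VEMD visits for the listed conditions ends in admission, an admissions-only extract loses 1 − *p* of them. The protocol does not give *p*, so no figure follows. Most of what remained would also be expected in VAED, given the stated capture above 95%.

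**Phase affected.** Section 4.6.1 says VAED and VEMD will not be used in the prospective phase. The rows under the prospective design therefore repeat the retrospective wording and do not widen the problem to a second phase of VEMD use.

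**The case against.** The best defence is that the protocol, read as a whole, already means all presentations. The inclusion criteria take every VEMD record, the only exclusion is unrelated, and the variable request uses the presentation date. The VEMD row repeats the VAED row's phrase and condition list, so carried-over wording is a plausible explanation. On this view there is a drafting slip and no exclusion.

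Most of this stands. A reader might infer from the extraction row that patients discharged home are definitely left out, and that the ED measure is a second copy of the admission measure. The documents do not support that. They contain a contradiction, and the weight of the other sections favours presentations. Nor does the protocol say that ED results will be used to confirm admission results. Some overlap with VAED would remain even if all presentations were included, because admitted ED patients would still be in both sources.

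Two further extensions also fail. RHEMMS is already worded as presentations, so it needs no change on this account. No objective requires a separate analysis of discharged patients.

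The defence does not remove the contradiction itself. The table is introduced as setting out the intended datasets, it is a natural place for a custodian to look for the scope, and there the wrong event is stated four times.

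**Conclusion.** The point holds as an internal contradiction about the scope of one data source. The extraction rows say admissions, while the row label, the secondary objective, the inclusion and exclusion criteria and the requested date field point to all ED presentations. This is a wrongly stated scope, and so not a detail that can be left to the statistical analysis plan.

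The consequence is conditional. Loss of discharged patients and heavy overlap with VAED follow only if the extraction row is applied literally. Their size cannot be derived from the protocol, and any percentage would rest on an admission share that it does not give. Site-specific ED data and RHEMMS are unaffected by the wording. The correction is worth making because VEMD is the statewide retrospective ED source and a mistaken extract would not be detectable from the variables requested.

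**What to change.** In all four VEMD rows (Sections 4.3.3 and 4.4.1.2), replace the reference to acute admissions with *presentations, whether admitted or discharged*. This brings the rows into line with the secondary objectives, Section 4.5.7 and the VEMD date field in Appendix 16.1. The cost is a wording change in one row that is printed four times. If an extract has already been taken on the narrower reading, it would have to be repeated and would be larger.

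Optionally, add ED departure status to the VEMD variable list in Appendix 16.1, so that the delivered scope can be checked. The cost is one more field, which has to be justified against the commitment in Section 9.2.1 to keep variables to those the objectives require. If the field is not wanted, written confirmation of scope from the custodian would serve the same purpose.
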